# Practices and challenges in the laboratory diagnosis of cryptococcosis in six hospitals in the three southern provinces of Mozambique.

This is a cross-sectional study with a mixed approach. The qualitative approach will be generic, where the current situation will be assessed before the intervention is implemented (Figure 2: Pre-implementation phase) in order to identify elements of the social, health, administrative, and structural context that may or may not favor the intervention in the local context.

The assessment of the current situation will be carried out in six hospitals (MCH, MGH, JMGH, MPH, XPH, and CHC) over three months. Sampling will be non-probabilistic, and intentional with regard to the participants and by convenience with regard to the study sites.

The data for this study will be obtained through semi-structured questionnaires (Annexes I, II, and IV) and interviews (Annex III) with health professionals from each hospital (clinicians from the medical service and microbiology laboratory technicians); and a list will be made of the equipment, existing material and a description of the cryptococcosis diagnoses currently carried out in each hospital involved in the study and to identify barriers and facilitators to implementing the technique of diagnosing cryptococcosis with urine samples.

The data will be analyzed using the R studio statistical package, where the following analyses will be carried out: descriptive analysis (calculating frequencies, mean or median, standard deviation, and variance); and chi-square to compare frequencies. The results will be described and presented in tables and graphs. A p-value of <0.05 will be considered significant.

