# To implement the technique of laboratory diagnosis of cryptococcosis using the China ink method in urine as a point of care in selected hospitals in three southern provinces of Mozambique.

This is a stepped wedge trial. Sampling will be non-probabilistic by convenience in relation to the study sites and purposive in relation to the participants.

The study will be carried out in six hospitals (MCH, MGH, JMGH, MPH, XPH, and CHC) over six months. The Adaptation Phase will be the beginning of the iteration with the new test, the healthcare professionals (clinicians in medical service and laboratory technicians assigned to the microbiology sector) adapt to the workflow associated with the intervention (Figure 2). During the three months of adaptation, the researcher will carry out training on the care, diagnosis and treatment of cryptococcosis using urine dye (5 to 20 ml of the sample) with intentionally selected healthcare professionals, the diagnostic guide tools will be provided and an information-sharing workflow will be established between the laboratory and the clinicians.

It's up to the clinician to decide which patients to ask for a urine sample to diagnose cryptococcosis and also to decide what clinical information to share with the laboratory according to each situation. We will provide the national health system with a resource for the diagnosis of cryptococcosis, instead of empirical treatment when routine treatment is not available. Therefore, the clinician is free to request routine or experimental testing. If the clinician decides to request a urine sample for the diagnosis of cryptococcosis, the laboratory will provide feedback according to the clinician's request in order to follow up on the patient.

The implementation of the diagnosis of cryptococcosis with Chinese ink using non-invasive urine samples at the selected sites will take place over 6 months. In this implementation phase, the health professionals assigned to the medical service with knowledge of the intervention (new test for cryptococcosis) will request that it be carried out by colleagues from the laboratory who have been previously trained in its execution. Throughout this phase (Figure 2) monitoring of clinicians' behaviour in relation to the use of the new diagnostic will take place and documentation of its implementation will be captured (Appendix V).

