# Evaluation of the RE-AIM-based implementation of the technique of laboratory diagnosis of cryptococcosis using the China ink method in urine as a point of care in southern Mozambique

This is a cross-sectional quantitative study aimed at measuring the contribution of the diagnosis introduced (intervention effect) in the six hospitals (MCH, MGH, JMGH, MPH, XPH and CHC) over three months. Sampling will be non-probabilistic, intentional with regard to the participants (healthcare professionals) and by convenience concerning the study sites.

In the Implementation Evaluation Phase (Post-implementation), during three months the implementation will be evaluated using the RE-AIM conceptual framework with five domains reach (comprehensiveness), effectiveness, adoption (acceptability and representativeness), implementation and maintenance (sustainability) of the intervention in the hospitals. Data collection will be based on previously prepared questionnaires and standardized scripts coupled to the REDCap platform loaded onto the tablet.

- Reach will be calculated through the proportion of individuals covered by the intervention (clinicians and laboratory technicians).
- Efficacy will be assessed by checking laboratory and clinical results, time to diagnosis and satisfaction of health professionals.

The study includes an evaluation at the beginning (baseline) pre-implementation and at the end post-implementation, where laboratory and clinical results, time to diagnosis and satisfaction of health professionals will be verified at both times. The efficacy of the intervention will therefore be evaluated before and after implementation. WHO recommendations will be consulted, which recommend screening and treatment to prevent complications from a cryptococcal infection. The test to be implemented will contribute to starting treatment on the same day as the consultation and based on the aetiological diagnosis.

- Adoption will be explored through the representativeness of the services that have adopted the implementation including sample flow, laboratory processing and feedback, use of scripts drawn up and made available during the intervention.
- A Likert scale will also be used to analyze the satisfaction of all health professionals covered by the intervention during the study period (clinicians and laboratory technicians).

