**(Práticas/conduta _Clínico)**

1. **Indique o principal método de diagnóstico de criptococoses em uso no seu laboratório**

Clinico ; Tinta da China ; CrAg ; Cultura ; Teste de aglutinação em latex (TAL) ; Ensaio imune enzimático (EIE); PCR

1. **Com que frequência solicitas o teste?**

Sempre As vezes**** Nunca Não sei ****

1. **Com que frequência o teste de *Criptococcus* esta disponível?**

Sempre As vezes**** Nunca Não sei ****

1. **Tempo de resposta do Laboratório** (forneça sua melhor estimativa)

______min _______horas

1. **Tempo de início de tratamento após o resultado positivo** (forneça sua melhor estimativa)

______horas ______dias

1. **Considera a criptococose uma doença negligenciada em Moçambique?**

Sim Não 

1. **Antes de solicitar o teste que factores considera? (**pode escolher mais do que uma resposta)

**** Gravidade da doença

 Carga do trabalho na clínica/laboratório

 Idade do Paciente

 Disponibilidade de serviços de laboratório

CD4<100cell/mm^3^

CD4<100cell/mm^3^

 Outro (Faz favor mencionar):____________________________________________

1. **Qual é a sua opinião sobre o formulário de solicitação dos enxames laboratoriais?**

Adequado  Inadequado 

1. **O laboratório notifica as enfermarias quando há introdução de um novo exame incluindo os seus parâmetros?**

Sim Não

1. **O laboratório notifica imediatamente os resultados críticos**

Sim Não

1. **Com que frequência o laboratório avisa a você quando há interrupção de um determinado exame?**

Sempre As vezes Nunca Não sei 

1. **Você sente que a qualidade do trabalho é consistente em todos os turnos? (horário de trabalho, fim de semana, feriado, plantão noturno)**

Sim Não

1. **Se NÃO, na sua opinião em qual turno a qualidade do serviço é comprometida?**

Horário de trabalho Fim de semana Feriado Plantão noturno

1. **Quantos pacientes assiste por semana? (forneça sua melhor estimativa)**

<10 10 - 20 ≥30

1. **Qual é o perfil do paciente que chega á US**

Crítico moderado

1. **Assinale os sinais/sintomas da criptococose que observas nos seus pacientes**

cefaleia febre rigidez da nuca convulsões acne

Outro (por favor mencione):__________________________

1. **Existem critérios para triagem?**

Sim  Não 

1. **Guião de definição de caso disponível**

Sim  Não 

1. **O rastreio de criptococose em pacientes HIV faz parte da rotina na sua US?**

Sim  Não 

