**QUESTIONÁRIO**

**Código ___ ___ ___/_______/_____/202___**

**AVALIAÇÃO DA INTERVENÇÃO**

**(Clinico)**

1. **As ferramentas disponibilizadas no treino são mais esclarecedores no âmbito de diagnóstico e tratamento da criptococose**

Concordo fortemente Concordo Neutro Descordo Descordo fortemente

1. **A intervenção é uma alternativa recomendável para triagem laboratorial da Criptococose**

Concordo fortemente Concordo Neutro Descordo Descordo fortemente

1. **Desde a sua implementação o teste da tinta-da-China a partir da urina esteve sempre disponível no Hospital**

Concordo fortemente Concordo Neutro Descordo Descordo fortemente

1. **Qualidade dos serviços melhorou com o novo diagnóstico laboratorial**

Concordo fortemente Concordo Neutro Descordo Descordo fortemente

1. **Pode-se estimar a percentagem de pacientes beneficiados pela intervenção em:**

 100%  80 – 99% 50 – 79%  <50%

1. **Avalie a sua satisfação em relação ao diagnostico laboratorial com a técnica da tinta da China usando a urina**

Muito satisfeito Satisfeito Neutro insatisfeito Muito insatisfeito

1. **Avalie a sua satisfação em relação a disponibilidade do pessoal do laboratório quando você tenta contatá-los?**

Muito satisfeito Satisfeito Neutro insatisfeito Muito insatisfeito

1. **Avalie a sua satisfação em relação ao tempo de resposta do laboratório**

Muito satisfeito Satisfeito Neutro insatisfeito Muito insatisfeito

1. **Avalie a sua satisfação em relação ao formulário de solicitação dos enxames laboratoriais**

Muito satisfeito Satisfeito Neutro insatisfeito Muito insatisfeito

1. **Avalie a sua satisfação em relação a clareza, legibilidade e integridade do resultado do laboratório relatório?**

Muito satisfeito Satisfeito Neutro insatisfeito Muito insatisfeito

1. **A qualidade do diagnóstico foi consistente em todos os turnos? (horário de trabalho, fim de semana, feriado, plantão noturno)**

Concordo fortemente Concordo Neutro Descordo Descordo fortemente

1. **Na sua opinião em qual turno, a qualidade do serviço do laboratório foi comprometida?**

Horário de trabalho Fim de semana Feriado Plantão noturno NA

1. **O número de pacientes internados devido a complicações associadas a meningite criptocócica reduziu com a introdução da nova abordagem do diagnóstico**

Concordo fortemente Concordo Neutro Descordo Descordo fortemente

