1. **Com a introdução da nova abordagem do diagnóstico o número de óbitos reduziu**

Concordo fortemente Concordo Neutro Descordo Descordo fortemente

1. **A nova abordagem do diagnóstico contribuiu para que maior número de indivíduos vivendo com HIV tivessem oportunidade de testar para *Criptococcus***

Concordo fortemente Concordo Neutro Descordo Descordo fortemente

1. **O tratamento de pacientes com meningite criptocócica melhorou com implementação da nova abordagem para diagnóstico laboratorial**

Concordo fortemente Concordo Neutro Descordo Descordo fortemente

1. **Avalie na generalidade a sua satisfação em relação a intervenção no seu hospital**

Muito satisfeito Satisfeito Neutro insatisfeito Muito insatisfeito

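### Efficacy is to be verified before and after implementation, but the annexed forms record none of its named components in the same form at both times, and satisfaction has no baseline at all

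*Protocol*

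**What the plan says.** The third sub-study in Section 7.9 of the Protocol (evaluation based on RE-AIM) assesses efficacy through laboratory and clinical results, time to diagnosis and staff satisfaction. It states that "laboratory and clinical results, time to diagnosis and satisfaction of health professionals will be verified at both times", and concludes: "The efficacy of the intervention will therefore be evaluated before and after implementation".

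The first sub-study, which is the pre-implementation assessment, takes its data from "semi-structured questionnaires (Annexes I, II, and IV) and interviews (Annex III) with health professionals from each hospital". The second sub-study cites the remaining annex for the implementation phase: "documentation of its implementation will be captured (Appendix V". Both versions of Annex V (clinician and laboratory technician) are headed as an evaluation of the intervention. The third sub-study cites no annex by number. It refers only to questionnaires and standardized scripts prepared beforehand.

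Two other places describe a further source. Section 7.1 says that quantitative data, including positive and negative results and response time, come from a questionnaire and from observation with a script. Section 7.8 mentions an observation guide. Neither the script nor the guide is among the annexes.

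**The concern.** A before-after comparison needs the same quantity, recorded on the same scale, at both times. If the forms are used as annexed, a change in satisfaction cannot be calculated because there is no baseline value. Response time would be a number before and a satisfaction rating after. An analysis plan cannot repair this later, because it cannot recover an answer that was never collected.

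The direction of the risk matters too. What the forms do collect afterwards is largely the opinion of staff who were trained in the technique. The Protocol's limitations section itself warns that respondents may answer to please the institution or the researcher. If those opinions were the only material available for efficacy, a favourable result would be hard to interpret.

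**Working it through.** No arithmetic beyond counting applies, and the Protocol gives no figure to reproduce. I set the items of Annexes I to IV (tied to baseline by the first sub-study) against both Annex V forms, for each component of efficacy that the third sub-study names. I take laboratory response time as the nearest item to time to diagnosis, since no form uses the latter term.

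| Component | Baseline, Annexes I-IV | After, Annex V | Same item and scale? |
| --- | --- | --- | --- |
| Satisfaction | No satisfaction item | Five-point items in both forms | No |
| Time to diagnosis | Response time in minutes/hours (Annexes II and IV); open estimate in the Annex III interview | Satisfaction with response time only: "Avalie a sua satisfação em relação ao tempo de resposta do laboratório" | No |
| Laboratory results | Banded share of suspected samples with Cryptococcus (Annex II) | No counterpart | No |
| Clinical results | No outcome item | Agreement that deaths fell ("Com a introdução da nova abordagem do diagnóstico o número de óbitos reduziu", both forms) and that admissions fell (clinician form only) | No |

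The count is 0 of 4, or 0 of 3 if laboratory and clinical results are taken as one component.

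**Nearest baseline items to satisfaction.** Annex IV asks clinicians about the availability of laboratory staff (yes/no) and about the request form (adequate/inadequate). Annex V puts both topics on a five-point satisfaction scale. The topics overlap, but the scales do not match.

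**What could have a baseline.** Each Annex V form has six satisfaction items. In the clinician form, two concern the intervention (the urine technique, and the intervention overall). The other four do not: laboratory staff availability, response time, request form, and clarity of the result. The technician form also divides into two and four, with clinician availability and clarity of requests in place of the first and last of those four topics. So 6 - 2 = 4 items per form could be asked unchanged at baseline.

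**Time to treatment.** Annex IV asks it in hours or days ("Tempo de início de tratamento após o resultado positivo"), and Annex V does not ask it. The third sub-study does not name it as an efficacy component. However, the variables table lists the start of treatment after a positive test under the evaluation objective.

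**Does the variables table settle the matter?** It lists response time under the implementation objective only, not under the baseline or evaluation objective. It lists satisfaction under none of the three.

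**Near match set aside.** The question on which shift has poorer quality has almost the same options at both times, but it is not one of the named efficacy measures.

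**The case against.** The strongest reply is that the annexed questionnaires are not the only declared source. Section 7.1 names positive results, negative results and response time as data obtained partly by observation, Section 7.8 mentions a guide, and the third sub-study mentions scripts. Two of the four components may therefore have a second source. This stands. A reader might infer from the forms that no before-after efficacy measure can be calculated, or that the whole efficacy conclusion would rest on opinions given afterwards. The Protocol does not support that reading. What can be said is that the script is not shown and that its use at both times is not stated. It could not readily supply baseline satisfaction.

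Second, nothing forbids giving Annexes II and IV again after implementation, and the promise to verify at both times could be read as implying it. That is fair, but no repeat is planned anywhere. The text ties those annexes to the pre-implementation assessment.

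Third, satisfaction with the intervention cannot exist before the intervention. This is correct. For those items the remedy is to correct the wording, since no baseline question could be written.

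Fourth, the Protocol never calls the deaths and admissions items efficacy, and time to treatment is not a named component. Both points stand. A reader might take those opinion items as the Protocol's definition of clinical results, but it makes no such statement. They are only the nearest thing to clinical results that the Annex V forms contain.

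**Conclusion.** The concern holds for the annexed forms. None of the four named components is asked there in the same form at both times. The gap is clearest for satisfaction, which is promised at both times, asked only afterwards, and has no other plausible source. For laboratory results and response time, the finding is that a comparable before-after source is not shown. Whether one exists depends on the observation script. For clinical results, the forms hold only perceptions recorded after implementation.

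This rests on two assumptions: that Annex V is the post-implementation questionnaire, as its heading indicates, and that Annexes I to IV are not repeated, since no repeat is planned.

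This should be fixed. It stops short of an essential correction because efficacy is one of five RE-AIM domains and some components may be recoverable from observation.

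**What to change.** 1. Add the numeric response-time items of Annexes II and IV, unchanged, to the technician and clinician versions of Annex V respectively. Add the Annex IV time-to-treatment item to the clinician version, because the variables table lists treatment initiation for the evaluation.
2. Add the Annex V satisfaction items that do not name the intervention to the baseline forms on the same five-point scale. For clinicians these are laboratory staff availability, response time, request form and clarity of results. For technicians they are the corresponding items of their own form.
3. Restrict the claim of verification at both times to measures collected in the same form at both times. Report satisfaction with the intervention itself as post-only. If baseline collection is already complete, withdraw the before-after satisfaction claim.
4. Annex the observation script and state that it is used at both times for positive and negative results and for response time. Use the laboratory register only where one exists, since Annex II still asks whether it does.
5. Report the deaths and admissions items as staff perception.

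The form changes are small: two items more in the clinician Annex V, one in the technician Annex V, and four in each of the two baseline questionnaires (Annexes II and IV), plus a REDCap update. Any extraction from registers would be extra work that this does not cover, and its size cannot be judged from the Protocol.

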# Methods

## Study design and type

The study design is a stepped wedge trial with a mixed approach. Stepped wedge studies are prospective and intervention studies. The main characteristic of these studies is that the researcher sets up the implementation in phases, monitors the conditions of the intervention, and makes it possible to assess the effectiveness of the intervention tool or technique implemented. This type of study ensures that all selected study sites eventually receive the intervention and generally provides more reliable evidence (See Table 1).

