**Quantitative data analysis**

Quantitative data will be analyzed using the R studio statistical package. Univariate descriptive analyses will be carried out (mean or median age, standard deviation and variance will be calculated), percentage frequencies of the following variables: tests requested, doctors/laboratory technicians who adhered to the intervention, chi-square to check for associations between the intervention/test and the variables (level of education of the professional, availability of the test, severity of the disease and gender) and logistic regression to estimate the relationship between adherence to the test and factors severity of the disease, work overload in the US/laboratory, level of education of the professional, shift, gender, availability of laboratory services.

A Likert scale will be used to assess the level of satisfaction of all those involved in the intervention (doctors and laboratory technicians) during the study period. And the frequencies of the information obtained will be calculated.

The results will be described and presented in tables and graphs using the Microsoft Excel program. A p-value of <0.05 will be considered significant.

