The data will be analysed using the R studio statistical package. The frequencies of the variables (number of tests requested with and without feedback, number of trained professionals) will be calculated and the frequencies will be compared using the Chi-square test.

The correlation between (number of professionals trained and number of tests requested) will be determined; the Odds Ratio (OR) will be estimated using regression: services covered/improved (dependent variable) and independent variables: professional trained, years of practice, level of education of the professional; age, gender.

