- During implementation, the fidelity of health professionals in relation to the diagnosis, care and treatment of cryptococcosis based on documented observation will be assessed.
- Maintenance (sustainability) will be assessed based on the simplicity of the intervention (laboratory diagnostic technique for cryptococcosis using urine), the workflow and the cost of the test implemented.

The data obtained in this study will be entered into the R studio statistical package, where the following analyses will be performed: Descriptive analysis (calculate frequencies, mean and variance), Chi-square to compare frequencies and multivariate regression to estimate the “Odds Ratio” (OR).

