# Study limitation

Some limitations were identified, namely:

- The nature of the stepped wedge study, which is long and involves following up participants, poses a risk of losing participants, introducing bias into the analysis of outcomes;

To minimize this fact, all clinicians from the medical service and laboratory technicians from the microbiology sector will be involved in the training and cross-sectional analyses of the outcomes will be carried out.

- Data collection through self-administered questionnaires is likely to be a limitation because participants may respond to please the institution and its managers, and using interviews to collect qualitative data risks participants responding in a way they think is appropriate. the researcher wants to hear;

To minimize this fact, the questionnaires will be anonymous, the researcher will be present when the questionnaire is administered and during the interviews to clarify the interviewee regarding the questions.

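### Efficacy is judged as baseline against end, so the declared stepped wedge cannot separate the intervention from calendar time

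*Protocol*

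**What the plan says.** Under Study design and type (7.1): "The study design is a stepped wedge trial with a mixed approach". Table 1 staggers six hospitals over 15 months, with cells marked control (C), pre-implementation (PI), adaptation (AD), implementation (I) and follow-up (FU), and some cells left blank.

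The third sub-study, the RE-AIM evaluation, carries the effect claim: "This is a cross-sectional quantitative study aimed at measuring the contribution of the diagnosis introduced (intervention effect"). Its data come from two occasions: "The study includes an evaluation at the beginning (baseline) pre-implementation and at the end post-implementation". It concludes: "The efficacy of the intervention will therefore be evaluated before and after implementation". Efficacy there covers laboratory and clinical results, time to diagnosis and staff satisfaction.

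The analysis named for this sub-study is "Chi-square to compare frequencies and multivariate regression to estimate the" odds ratio. For sub-study 2, "the frequencies will be compared using the Chi-square test". The section Study limitation adds that "cross-sectional analyses of the outcomes will be carried out". The decision rule under Quantitative data analysis is "A p-value of <0.05 will be considered significant".

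The regressions listed in the sub-study texts and in the table Variables and data analysis plan model adherence to testing, test requests or services covered. Their covariates include the health unit (US) for sub-study 3 and hospital level for sub-study 2. None includes calendar time, a before/after indicator or exposure status.

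**The concern.** A stepped wedge earns its value from months in which some hospitals have started and others have not; those months allow a background trend to be estimated and removed. Comparing the start with the end discards exactly those months. What remains is an uncontrolled before-after comparison, although the protocol describes the design as one that generally gives more reliable evidence.

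This matters here because the background is unlikely to be still. The Motivation section reports interruptions in the supply of rapid tests. If that supply recovered or worsened over 15 months, testing volumes and time to diagnosis would move with no contribution from the urine test. The results are meant for advocacy with the Ministry of Health, so a supply change read as an intervention effect would carry weight.

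**Working it through.** **Inputs from the protocol.** Significance level 0.05; six hospitals and 15 months (Table 1); evaluation in a final three-month phase (Study timeline); staff listed under Sample and Sampling: clinicians 8+4+4+3+3+2 = 24, technicians 6×2 = 12, total 36.

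**Inputs not in the protocol, assumed.** Baseline proportion 50%; background drift 0 to 20 percentage points; no true effect. No power, effect size, intracluster correlation or trend is given, so apart from the threshold there is no planned figure to reproduce. As a reference, a chi-square on 36 against 36 independent answers with no drift rejects in 0.046 of simulations.

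**Step 1: can two windows identify the effect?** Take months 1–3 and 13–15. The model has 6 hospital + 5 month + 1 exposure = 12 columns. Every hospital is C in months 1–3 and FU in months 13–15, so the exposure column equals the sum of the indicators for months 13, 14 and 15. Rank is 11: the effect is not estimable. If the baseline is taken instead from the PI months (5, 6 or 7, by hospital), the result is the same, because no calendar month then contains both a baseline and an end record.

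**Step 2: what can a drift do to the test?** With n = 36 per occasion, p₁ = 0.5, p₂ = 0.5 + δ and mean p̄, the chance of declaring an improvement is

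Φ[(δ − 1.96·SE₀)/SE₁], where SE₀ = √(2p̄(1−p̄)/n) and SE₁ = √((p₁(1−p₁)+p₂(1−p₂))/n).

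For δ = 0.10: SE₀ = √(2×0.55×0.45/36) = 0.1173; SE₁ = √((0.25+0.24)/36) = 0.1167; (0.10 − 0.2298)/0.1167 = −1.113; Φ = 0.133.

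| Drift, no true effect | Formula (upper tail) | Simulated, 36 v 36 | Simulated, 240 v 240 |
|---|---|---|---|
| 5 points | 0.062 | 0.065 | 0.20 |
| 10 points | 0.133 | 0.13 | 0.59 |
| 15 points | 0.248 | 0.24 | 0.91 |
| 20 points | 0.408 | 0.41 | 0.995 |

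The last column assumes 10 requests for each of 24 clinicians per occasion (24×10 = 240). More records make the false signal more certain.

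**Step 3: does clustering add to it?** With no drift but hospital-by-period variation of SD 0.25, 0.5 or 0.75 on the logit scale (assumed), the 36 v 36 chi-square rejects at 0.056, 0.082 and 0.121.

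**Step 4: do the 15 months allow a repair?** The full model has 6 + 14 + 1 = 21 columns. Using only C cells against I and FU cells (30 + 6 + 33 = 69 cells), rank is 20. C ends in month 6 and I begins in month 7, so exposure again equals a sum of month indicators. Counting the six PI cells as unexposed (75 cells) gives rank 21. The only month with a contrast is then month 7: MCH exposed, XPH and CHC unexposed. Counting PI, AD and blank cells as unexposed (90 cells) gives contrasts in months 7 to 11, with 1, 2, 3, 4 and 5 of six hospitals exposed.

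**Step 5: does the repair hold the level?** Weighted least squares on hospital-month proportions, with hospital and month effects and all 90 cells, gives simulated type I error of 0.048–0.058 for drifts of 0, 10 and 20 points. A pooled chi-square on the same data gives 0.12–0.14, 0.39–0.40 and 0.81–0.83.

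**The case against.** Four objections deserve weight.

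*Hospital is not ignored throughout.* A reader might infer that every analysis pools the hospitals. The documents do not support that: the sub-study 3 regression lists US, which the abbreviations define as the health unit, and the sub-study 2 table lists hospital level. This stands. It does not rescue the effect estimate, because those regressions have no exposure or period term.

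*The chi-square is not tied to the before-after contrast.* Where the protocol names pairs of variables for the chi-square, they are others, such as test request against laboratory feedback or staff characteristics against type of test. This also stands. The chi-square is simply the only generic test left that could carry the contrast, and the confounding in step 1 applies whichever test is used.

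*Random effects and small-sample corrections usually belong in an analysis plan.* True. But the comparison of baseline with end, and the cross-sectional treatment of outcomes, are fixed in the protocol. An analysis plan could replace them only by contradicting it.

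*The error rates rest on assumed inputs.* They do. With the 36 listed staff and a small drift, inflation is slight. The rank results need only Table 1 and the two evaluation windows.

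**Conclusion.** The point holds and should be fixed before analysis. As written, the effect comparison is an uncontrolled before-after contrast inside a declared stepped wedge, and it cannot distinguish the intervention from anything else that changed over the period. That conclusion needs no assumed parameter. Its size does: about 6 to 7%, 13% and 41% false positives for drifts of 5, 10 and 20 points, assuming a 50% baseline, 36 independent answers per occasion and no true effect.

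Two stronger readings are not supported. A reader might infer that treating the same staff as independent at both occasions inflates the error. It does the reverse: simulated rates fall to 0.029, 0.012 and 0.004 for between-staff SDs of 1, 2 and 3 on the logit scale. A reader might also infer that the effect measure is the count of urine India ink tests, which would be zero before implementation by construction. The protocol lists that count as a variable but does not include it in its definition of efficacy, and types of test requested are recorded as well.

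**What to change.** In the RE-AIM sub-study and the table Variables and data analysis plan:

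1. For laboratory outcomes, such as cryptococcosis tests by any method with a result returned and time to result, replace the before-after contrast with a hospital-by-month analysis over all 15 months. Include fixed month effects, a hospital effect and an exposure term (I and FU exposed).
2. State how PI, AD and blank cells are classed. PI cells, at least, must count as unexposed for the effect to be estimable; with PI alone it rests on month 7. Because training takes place during adaptation, add a sensitivity analysis that classes AD and blank cells differently, and say how few months then inform it.
3. Use small-sample or permutation-type inference for six hospitals. The protocol describes no random roll-out order, so permutation inference is approximate and hospital-specific trends remain a limitation.
4. Report staff questionnaire and satisfaction items descriptively, without an effect claim: the satisfaction scales appear only in the post-implementation Annex V, with no matching baseline scale. Do the same for any outcome whose monthly counts cannot be obtained.

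The cost is extraction of monthly aggregate counts at each site, a revised analysis text and wider confidence intervals. Feasibility must be checked first, since Annex II still asks whether each laboratory keeps a register or a working database.
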